#### Model Descriptions

We will train and evaluate 4 different ML classifiers, a multiple logistic regression (LogReg) classifier using elastic net, a random forest (RF) classifier, a support vector machine (SVM) classifier, and an AdaBoost classifier. For a review of the models used, see the textbook by Geron [79]. In short, the LogReg classifier works by modeling the probability of a binary outcome based on one or more predictor variables, using the logistic function to ensure the output is between 0 and 1. We will use elastic net regularization to facilitate feature selection and prevent overfitting. Elastic net combines L1 (lasso) and L2 (ridge) penalties, encouraging sparsity and maintaining stability in the model. The RF classifier works by building multiple decision trees on random subsets of data and predictors. Each tree’s prediction is based on splits that minimize variance in the target variable, with the final model ensembling these predictions. The SVM classifier works by finding the hyperplane that maximizes the margin between different classes in the feature space. SVM is particularly effective in high-dimensional spaces and when the number of dimensions exceeds the number of samples. AdaBoost, the final classifier, works by combining multiple weak classifiers, typically decision trees, into a single strong classifier. It sequentially fits these weak learners on repeatedly modified versions of the data, focusing more on misclassified instances to improve overall accuracy.

#### Hyperparameter Tuning

We will conduct 5-fold cross-validation using randomized search for hyperparameter tuning and training evaluation to enhance the external generalizability and robustness of the results. This process involves defining a hyperparameter space, then randomly selecting a predetermined number of samples—in this case, 10—from this space, and conducting 5-fold cross-validation for each selected set of hyperparameters. Fivefold cross-validation is done by partitioning the data into 5 subsets, training the model on 4 subsets, and validating it on the remaining subset. This process is repeated 5 times, with each subset used exactly once as the validation data. The best performing hyperparameters will be chosen for the final models that are trained and then evaluated on the test set.

The hyperparameter ranges for the LogReg will include C values from 0.01 to 100 and l1_ratio values from 0 to 1. For RF, the parameter ranges will include the number of estimators from 5 to 1200, minimum samples required to split a node from 10 to 200, maximum depths from 5 to 750, and a binary indicator for bootstrapping. For SVM, the parameter range for the randomized search will include regularization parameter C values from 0.01 to 1 and for AdaBoost, the parameter ranges for the randomized search will include the number of estimators, ranging from 1 to 1500, and learning rates from 0.001 to 2.5.

#### Model Interpretation

The models developed to identify the responder status will be evaluated using BACC, precision and recall, both in the training set obtained through k-fold cross-validation and in the test set. Predictor importance in the RF model will be determined using Scikit-learn’s Feature importance function, which quantifies each predictor’s contribution to the model’s balanced classification accuracy. Area under the curve will be used to assess the models’ capability to distinguish between classes accurately. The approach will aim to provide a clear understanding of the models’ effectiveness and the role of various predictors. Our primary outcome of interest for comparison will be BACC in each model in the test set with the aim that (1) the model should perform better than a dummy model that simply predicts the most common responder status, and (2) that the model should perform 67% BACC or above to be deemed clinically useful [28]. Furthermore, the models will be statistically compared using bootstrap sampling. Specifically, we will generate 5000 bootstrap samples from the test set, calculating the BACC for each model on each sample. The distributions of these bootstrap BACCs will be compared and we will conclude that there is a statistically significant difference between models if the CIs do not overlap.

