## Methods

### Study Design

We will use collected data from a randomized controlled trial (RCT; N=300) of internet-delivered CBT for patients diagnosed with AD or ED compared to an active, internet-delivered control condition consisting of general health-promoting advice. A priori power analysis conducted for the main outcome in the RCT indicated that 300 study participants would be needed for a 90% power to detect a between-group effect size of Cohen *d*=0.4 with a significance level of .05 and an expected attrition rate of 10%. Due to the limited sample size and general lack of knowledge on predictors of treatment effect, prediction models in this study will be based on pooled data from both treatment arms. The study design is prospective, and predictors will include sociodemographic and clinical information, clinician-assessed data, self-rated symptoms, and results from cognitive test scores. The results will be reported in line with the TRIPOD+AI (Transparent Reporting of a Multivariable Prediction Model for Individual Prognosis or Diagnosis+Artificial Intelligence) statement [30].

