### Procedure

#### Participants

In total, 300 nationally recruited individuals were diagnosed with a primary diagnosis of AD (n=142, 47.3%) or ED (n=158, 52.7%) and were included in the RCT. Participant recruitment was carried out through social media, newspaper advertisements, and information provided to health care clinics. Participants self-referred to the study web page, where they signed digital informed consent and completed a screening battery consisting of sociodemographic and clinical background questions as well as self-report symptom questionnaires. Participants were subsequently clinically assessed by a psychologist using a structured diagnostic interview, including Mini International Neuropsychiatric Interview [31], self-rated ED [32], and the Adjustment Disorder New Module-8 (ADNM-8) [33]. For inclusion, participants needed to (1) fulfill the criteria for a primary diagnosis of AD or ED, (2) be aged between 18 and 65 years, (3) have regular access to a computer with internet access, and (4) be able to read and write in the Swedish language. Exclusion criteria included (1) drug use or addiction during the past 6 months, (2) current or past psychosis or bipolar disorder, (3) current risk of suicide, (4) changed psychopharmacological treatment in the past month, (5) other ongoing psychological treatment, and (6) previous experience of CBT for AD or ED in the past year.

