#### Data Cleaning and Preparation

We will transform categorical variables into a format suitable for numerical analysis. For binary categorical variables, we will use label encoding. For multinomial variables, we will apply one-hot encoding. In addition, for ordinal data, which have a natural order, we will transform the categories into integers.

Predictor variables with over 20% missing data will be excluded from the analysis. Categorical variables exhibiting low variance, as determined by predictors with <5% of a certain response will be removed. For instance, by removing the variable “Sleep medication” if it only occurs in 3 out of 300 patients. This approach aims to reduce unnecessary complexity in the predictions and to minimize the risk of overfitting. To control for multicollinearity, variables with a correlation coefficient ≥0.8 will be removed from the traditional prediction analysis but will be retained for the ML model development. Data that are highly skewed will be transformed if deemed appropriate.

Cognitive test results will be manually reviewed before model fitting to validate a proper result. Comments pertaining to technical difficulties and disturbances that may have affected the test result will be assessed by two of the authors and lead to exclusion if so judged. Participants who have noted during screening that Swedish is not their native language will be excluded from the analysis for CERAD and FAS. We will standardize the raw scores from the cognitive tests using normative regression models with age, education and sex as covariates. This standardization process will convert raw scores into *Z* scores, as previously described by Franke Foyen et al [62] and for a full overview of the multiple linear regression models used and how they were calculated, see the studies by Mindmore [77] and van den Hurk et al [78].

Patients who have missing data for the posttreatment PSS-10, ie, the missing outcome variable for the primary aim, will be replaced by a PSS-10 process measurement at week 10 if available; If not, the patient will be excluded from the analysis. The number of participants excluded from the final models will be described.

To prepare our primary outcome, RCI for the PSS-10 before to after treatment will be computed using the following formula [39]:

Cronbach α=0.83 from normative data will be used [38]. Patients exhibiting an RCI of −1.96 will be classified as responders.

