#### Train Test Split

As the ultimate goal of any model is to predict an outcome in unseen data, the ML models will be developed using a training set, and then evaluated on a test set stratified on main diagnosis (AD or ED) and responder status. In total, 70% of the data will be used for selecting predictor variables and training the models, and 30% for testing the prediction accuracy of the models. The choice of 70 to 30 was due to the limited size of our sample, as fewer observations in the testing data makes it difficult to use uncommon predictors. No external validation set is currently available at the time of writing.

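### The random forest importance function named in the protocol measures impurity reduction in the training data, not the contribution to balanced accuracy that the protocol attributes to it

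*Protocol article*

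**What the plan says.** Under Model Interpretation, the protocol article says "Predictor importance in the RF model will be determined using Scikit-learn’s Feature importance function". The same sentence describes the result as each predictor's contribution to balanced classification accuracy. The section names no other importance measure for the machine learning models. Strengths and Limitations looks to importance measures to offset the poor interpretability of models such as the random forest.

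Model Descriptions says the forest's trees choose splits that minimise variance in the target, which is an impurity criterion.

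Hyperparameter Tuning gives the random forest ranges as "minimum samples required to split a node from 10 to 200, maximum depths from 5 to 750", together with the number of trees and a bootstrap on/off setting. The search works by "randomly selecting a predetermined number of samples—in this case, 10—from this space", and each draw is assessed by 5-fold cross-validation, "training the model on 4 subsets, and validating it on the remaining subset". The best draw is kept. Train Test Split says "70% of the data will be used for selecting predictor variables and training the models, and 30% for testing".

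**The concern.** The tool and the description do not match. A reader of the results would take the ranking to show which predictors help to classify patients correctly, with responders and nonresponders weighted equally. The named function shows something else: how much each predictor was used to purify nodes in the data on which the trees were grown.

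The difference matters with this predictor set. Table 1 has 12 two-category rows (sex, native speaker, four medication types, primary diagnosis, four secondary diagnoses, ADNM-8 criteria). One-hot encoding of relationship status (3), employment status (8), employment type (11) and stressors (16) adds up to 38 further 0/1 columns before the rare ones are removed. These stand beside symptom scales and cognitive scores with many distinct values. A many-valued predictor offers many cut points at each node and so more chances of a lucky split; a 0/1 column offers one. A binary clinical fact that truly predicts response could rank below scales that carry no signal.

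A smaller matter is the tuning range. A node can be split only if it holds at least the minimum number of patients, and the upper limit of 200 is larger than the data on which a cross-validation fit is made.

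**Working it through.** **1. What the named function computes.** The documentation of the random forest's `feature_importances_` was read in an installed copy of scikit-learn (version 1.9.0). It calls the values impurity-based, defines them as the normalised total reduction of the split criterion (Gini importance), warns that they can mislead for features with many unique values, and points to `permutation_importance` as an alternative. With responder share p in a node, Gini impurity is 2p(1 − p), twice the variance p(1 − p), so this agrees with the criterion in Model Descriptions. Balanced accuracy is (sensitivity + specificity)/2 and requires predicted classes set against observed ones. Nothing of that kind enters the impurity sum.

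**2. Size of the tilt towards many-valued predictors.** These are simulations under assumed inputs, not trial data.
- Pure noise, n = 189, 20 continuous and 20 binary predictors: continuous predictors received about 9 times the importance of binary ones (8.6 to 9 over separate runs). In one set of 40 repeats, every top-10 place went to a continuous variable.
- One binary predictor with a true odds ratio of 2.5 among 30 continuous and 19 binary noise predictors, n = 210, 40 repeats: its median rank was 31 of 50.

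**3. Sample sizes.** The trial's own figure was reproduced first. From "90% power to detect a between-group effect size of Cohen *d*=0.4 with a significance level of .05 and an expected attrition rate of 10" (two-sided test and equal arms assumed), n per arm = 2(1.960 + 1.282)²/0.4² = 131.4, so 132 per arm and 264 in total; 264/0.9 = 293.3, so 294, in line with the 300 recruited. Patients without a usable outcome are dropped ("If not, the patient will be excluded from the analysis"). Their number is not given, so N = 270 (10% missing) is an assumption beside N = 300.

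**4. Share of minimum-split values that cannot split.** The range 10 to 200 holds 191 integers; uniform draws are assumed. Without bootstrapping, the root node holds the whole fit set. With it, scikit-learn counts distinct patients at the root, on average about 63% of the fit set.

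| | N = 300 | N = 270 |
|---|---|---|
| Training set, 0.7 × N | 210 | 189 |
| Cross-validation fit, 0.8 × training | 168 | 151 |
| No bootstrap: values above fit size | 169–200: 32/191 = 16.8% | 152–200: 49/191 = 25.7% |
| Bootstrap: mean distinct patients | 106.4 | 95.6 |
| Bootstrap: values above that mean | 107–200: 94/191 = 49.2% | 96–200: 105/191 = 55.0% |
| Bootstrap on for half the draws | 33.0%, or 3.3 of 10 | 40.3%, or 4.0 of 10 |

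Under a stricter rule, that no tree in the forest splits at all, the bootstrap limits are about 118 (83/191 = 43.5%) and 107 (94/191 = 49.2%). The mixed shares become (16.8 + 43.5)/2 = 30.2% and (25.7 + 49.2)/2 = 37.5%. Either way, about 3 to 4 of the 10 draws are lost.

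Test fits on 168 simulated patients agreed. Without bootstrapping, every tree split at 168 and none at 169. With it, all split at 90, 64% at 105 and none at 120.

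**5. Chance that all 10 draws fail.** 0.330^10 ≈ 0.0015% at N = 300; 0.403^10 ≈ 0.011% at N = 270.

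**The case against.** *On importance.* The name in the protocol is loose, and permutation importance scored on balanced accuracy may have been meant. That is possible, but the sentence would then name the wrong tool, so it needs correcting on either reading. It is also fair to say that the ranking is secondary. The primary comparison is test-set balanced accuracy, which importance does not enter, and predictor identification rests mainly on the univariate regressions and the ablation study. The ratio of about 9 comes from pure noise and does not measure the distortion where there is real signal. All of this stands; it limits the weight of the point without removing it.

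*On tuning.* A reader might infer that the split range invalidates the random forest or handicaps it against the other three classifiers. The documents do not support that. Only the best draw is kept, and a forest that cannot split predicts one class and has balanced accuracy 0.50. If the search is scored on balanced accuracy, such a draw loses to any draw that performs better than that. In one simulated scenario (189 training patients, 50 predictors, 24 replicates, trees capped at 300), the protocol's ranges with 10 draws gave a mean test balanced accuracy of 0.598. Narrower ranges with 40 draws gave 0.600, a difference of 0.002 (SE 0.003). One scenario proves little in general, but nothing points to a material loss. The choice of 10 draws and the wide depth range are matters of preference.

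**Conclusion.** The importance sentence is wrong as written and should be fixed. The named function reports normalised Gini reduction in the training data, contains no balanced accuracy, and by construction favours many-valued scales over the yes/no items in Table 1. That it does so is certain; by how much in these data is unknown, and the ratio of about 9 to 1 is an illustration. The software check was made in scikit-learn 1.9.0.

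The split range is a minor note. Its upper end exceeds the cross-validation fit size by 32 at N = 300 and by 49 at N = 270. About 3 to 4 of 10 draws are wasted, assuming uniform integer draws and bootstrapping on for half of them, neither of which the article states. Fit size alone accounts for 1.7 to 2.6 draws; bootstrapping accounts for the rest. This leaves a smaller effective search, and it is not shown to bias the final model or the model comparison.

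**What to change.** **Importance (should-fix).** In Model Interpretation, replace the named function with permutation importance scored on balanced accuracy in held-out data (the cross-validation validation folds or the test set), with repeats. Add that strongly correlated scales share importance and must be read with care; this matters because variables correlated at 0.8 or above are kept for the machine learning models. The existing description of what is measured can then stand. If impurity importance is kept, describe it as that and state its tilt towards many-valued predictors.

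**Tuning range (minor).** In Hyperparameter Tuning, lower the upper limit of the minimum split below the number of patients at the root node of a cross-validation fit, allowing for bootstrapping, and state that the search is scored on balanced accuracy. The second part is useful because the article does not name the search score: under plain accuracy, a one-class forest would earn the majority share and might compete.

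The cost is two or three sentences and a little computing time. The article reports that the data had not been analysed for this study as of March 2025, so a change made before analysis carries no risk of being driven by results.

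### Classifiers are judged on test-set balanced accuracy, but no class weighting or cut-off is matched to it, so with clearly unequal classes a model of AUC near 0.75 can miss 67%

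*Protocol article*

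**What the plan says.** Model Interpretation sets the criterion: "Our primary outcome of interest for comparison will be BACC in each model in the test set". Two conditions are attached to it: "the model should perform better than a dummy model that simply predicts the most common responder status" and "the model should perform 67% BACC or above to be deemed clinically useful".

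Hyperparameter Tuning describes a randomized search with 5-fold cross-validation, "randomly selecting a predetermined number of samples—in this case, 10—from this space", and gives numeric ranges for all four classifiers. For logistic regression: "The hyperparameter ranges for the LogReg will include C values from 0.01 to 100 and l1_ratio values from 0 to 1". For random forest (RF) they cover number of trees, minimum split size, depth and bootstrapping; for the support vector machine (SVM), C; for AdaBoost, number of estimators and learning rate. No range contains a class weight, and no resampling or classification cut-off is mentioned. Selection is described as "The best performing hyperparameters will be chosen for the final models that are trained and then evaluated on the test set", without naming the score.

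Model Interpretation also says that the models are "evaluated using BACC, precision and recall, both in the training set obtained through k-fold cross-validation and in the test set", and that AUC will be assessed. Train Test Split stratifies on diagnosis and responder status. No expected responder share is given.

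**The concern.** BACC is the mean of sensitivity and specificity, so both classes count equally whatever their size. A classifier fitted with equal patient weights and cut at probability 0.5 (or decision value 0) instead aims at overall accuracy, which favours the larger class. When classes are equal the two aims coincide. When they are not, the default cut buys specificity at the cost of sensitivity for the smaller class, and BACC falls although discrimination is unchanged. The stratified split keeps the class ratio the same in both sets; it does not correct the ratio.

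Two conclusions are exposed. The usefulness verdict could be negative for a model that separates responders from nonresponders well enough. And the planned bootstrap comparison of BACC between models could partly compare how each algorithm reacts to imbalance at its default cut.

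**Working it through.** The article gives no figure on this point to reproduce. The majority-class dummy has BACC (1 + 0)/2 = 0.50 by definition, and the bar is 0.67.

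**Responder share (assumed).** The reliable change formula is not visible in the text at hand. If it is the standard one, the article's reliability of 0.83 means that response needs a fall of 1.96 × √(2 × 0.17) = 1.14 reference SD. With assumed mean falls of 0.4 to 1.6 SD and SD of change of 0.9 to 1.3, the share runs from about 20% (1 − Φ((1.14 − 0.4)/0.9)) to about 69% (1 − Φ((1.14 − 1.6)/0.9)). Near-equal and clearly unequal classes are both possible.

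**Expected BACC (equal-variance binormal model, calibrated scores).** With minority share p:

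- d′ = √2 × Φ⁻¹(AUC) and c = ln((1 − p)/p)/d′
- at the 0.5 cut: sensitivity = Φ(d′/2 − c), specificity = Φ(d′/2 + c), and BACC is their mean
- at the class-balanced cut: BACC = Φ(d′/2), whatever p is

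For AUC 0.75, d′ = 1.414 × 0.6745 = 0.954, so the balanced cut gives Φ(0.477) = 0.683. At p = 0.30, c = 0.847/0.954 = 0.888. Sensitivity is Φ(−0.411) = 0.340, specificity is Φ(1.365) = 0.914, and BACC is 0.627.

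| Minority share | AUC 0.75, 0.5 cut | AUC 0.75, balanced cut | AUC 0.80, 0.5 cut | AUC 0.80, balanced cut | AUC needed for 0.67 at the 0.5 cut |
|---|---|---|---|---|---|
| 50% | 0.683 | 0.683 | 0.724 | 0.724 | 0.733 |
| 40% | 0.669 | 0.683 | 0.713 | 0.724 | 0.752 |
| 35% | 0.651 | 0.683 | 0.699 | 0.724 | 0.770 |
| 30% | 0.627 | 0.683 | 0.679 | 0.724 | 0.791 |
| 20% | 0.569 | 0.683 | 0.623 | 0.724 | 0.839 |

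At the balanced cut, AUC 0.733 is enough at every share.

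**Chance of reaching 67% in the test set.** If all 300 patients are analysed, 30% is 90, or 27 and 63 at p = 0.30. With AUC 0.75:

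- 0.5 cut: SE = ½√(0.340 × 0.660/27 + 0.914 × 0.086/63) = 0.049, so P(BACC ≥ 0.67) = 1 − Φ((0.67 − 0.627)/0.049), about 19%.
- Balanced cut: SE = ½√(0.683 × 0.317 × (1/27 + 1/63)) = 0.054, so the chance is about 60%.

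**Simulation of the search.** Settings: 210 training patients; 44 predictors, four of them informative with joint AUC 0.85; 10 random draws; 5-fold cross-validation; scored on 2,000 new patients; 7 to 10 replicates (RF 4). Mean BACC at a 30% minority share:

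| Classifier | AUC, no weights, accuracy score | BACC, no weights, accuracy score | BACC, no weights, BACC score | BACC, balanced weights, BACC score |
|---|---|---|---|---|
| Logistic, elastic net | 0.833 | 0.695 | 0.707 | 0.764 |
| SVM | 0.801 | 0.579 | 0.579 | 0.726 |
| RF | 0.768 | 0.568 | 0.566 | 0.715 |

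Changing only the tuning score leaves SVM and RF where they were. The lead of logistic regression over SVM is 0.695 − 0.579 = 0.116 without weights and 0.764 − 0.726 = 0.038 with them. At 50:50, weighting made no material difference for any of the three.

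Limits: the predictors are invented, RF used 60 trees without tuning bootstrap, the SVM kernel was the software default, and AdaBoost was not simulated.

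**The case against.** The strongest reply is that the defaults are inferred from silence. The article states no cut-off and no equal weighting, does not call its search ranges exhaustive, and condenses a fuller plan. That is fair as far as missing detail goes. But the article names scikit-learn (or equivalent packages), lists numeric ranges classifier by classifier, and fixes a pass mark on BACC. Followed as written, that procedure does worse on its own criterion whenever classes are clearly unequal.

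A reader might infer that tuning ignores BACC. The text does not support this: the score is unnamed, and BACC is the first metric listed for the training cross-validation, so it may well be intended. The simulation shows that this half of the issue matters less in any case.

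A reader might also take "focusing more on misclassified instances to improve overall accuracy" as a declared accuracy target. It is a textbook description of how AdaBoost works, and AdaBoost reweights patients as it goes, so it cannot be said that all four methods weight every patient equally throughout.

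AUC, precision and recall are reported too, so a gap between discrimination and BACC would be visible. This stands, but the usefulness verdict rests on BACC.

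Finally, the size depends on assumptions. In a simulation with weaker signal (189 training patients, 92 columns, 30% responders), weighting raised logistic regression from 0.558 to 0.600 and RF from 0.516 to 0.554. Every classifier tried stayed below 0.67 either way, so no verdict changed.

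**Conclusion.** The point holds conditionally. The plan judges models on BACC without fixing a weighting or cut-off to match it, and leaves the tuning score unnamed. There is no loss near 50:50 and about 0.014 at a 40% minority share (0.683 − 0.669, AUC 0.75). At about 35% or less, a model with AUC near 0.75 loses 0.032 (35%) to 0.056 (30%), enough to put its expected BACC below 67%. In a 90-patient test set at 30%, its chance of passing is about 19% rather than 60%.

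A reader might conclude that unequal classes make good models fail. That is too strong: at 30%, AUC 0.80 still gives 0.679 in the binormal model, and unweighted logistic regression reached about 0.70 in simulation.

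The figures assume classification at the default cut, binormal calibrated scores for the formula, invented predictors for the simulation, and a responder share that the article does not give. Because that share is not given, the rule should be settled before the analysis.

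**What to change.** In Hyperparameter Tuning, name BACC as the score maximised in the 5-fold cross-validation. There or in Model Interpretation, add one rule for all four classifiers: the cut-off is chosen to maximise cross-validated BACC within the training set only and is applied unchanged to the test set. Alternatively, prespecify balanced class weights for logistic regression, RF and SVM and balanced sample weights for AdaBoost. Naming the score without one of these is not enough.

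The cost is about two sentences and one option per classifier. Overall accuracy will fall somewhat when classes are unequal, and probabilities from weighted fits need recalibration before they are reported as probabilities. The article says that the data had not been analysed for this study as of March 2025. If the analysis has still not been run, the rule can be fixed without knowledge of test-set results; choosing it afterwards would weaken the 67% verdict.

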**Results:**

All data were collected between April 2021 and September 2022. We hypothesize that key predictors will include younger age, education level, baseline symptom severity, treatment credibility, and history of sickness absence. We anticipate that the machine learning models will outperform a dummy model predicting the majority class and achieve a balanced accuracy of ≥67%, thus indicating clinical usefulness.

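### Both success criteria rest on a point estimate of balanced accuracy in about 81–90 test patients, with no allowance for sampling error and no rule for summarising four models

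*Protocol article*

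**What the plan says.** Under Model Interpretation, the protocol article makes test-set BACC, model by model, the main measure for comparison and sets two aims. The first is that "the model should perform better than a dummy model that simply predicts the most common responder status". The second is "that the model should perform 67% BACC or above to be deemed clinically useful". The abstract's Results paragraph makes the second aim a headline expectation: the models should "achieve a balanced accuracy of ≥67%, thus indicating clinical usefulness". Objective of the Study repeats it.

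Four classifiers are evaluated (Model Descriptions). Train Test Split reserves "30% for testing the prediction accuracy of the models".

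Model Interpretation also plans 5000 bootstrap samples of the test set. Their stated use is to compare models, with a difference declared when the intervals do not overlap. No interval is tied to either aim, and the text does not say whether the dummy is among the models compared.

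**The concern.** Both verdicts are read from a bare estimate in a small test set. A majority-class dummy has a BACC of exactly 0.50 whatever the responder rate, so the first aim amounts to an estimate above 0.50. The second aim attaches a consequential label to an estimate that could easily lie several points from the truth.

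Four models are also judged on the same patients, and no rule says which one carries the conclusion. At stake is the headline statement on clinical usefulness, which the Discussion links to later use of such models as decision-support tools. Because the article itself fixes the threshold, the measure and the purpose of the bootstrap, this is a weakness in what is written and not a detail left to another document.

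**Working it through.** **The plan's own figure.** The article gives no precision or power figure for BACC. Its only sample-size statement concerns the parent trial (Study Design): "300 study participants would be needed for a 90% power" at a "between-group effect size of Cohen *d*=0.4", alpha .05 and 10% attrition. Check, two-sided: n per arm = 2(1.960 + 1.282)²/0.4² = 131.3, so 132 per arm and 264 in total; 264/0.9 = 293.3, so 294. The t-test version gives 133 per arm, 266 in total and 296 after inflation. The stated 300 is reproduced to within 3%, but it does not address this question.

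**Test-set size.** 30% of 300 = 90. Under Data Cleaning and Preparation, a patient with no posttreatment PSS-10 is given the week-10 value if there is one. "If not, the patient will be excluded from the analysis" is the rule otherwise. If the full 10% were lost (assumption), 270 remain and 30% of 270 = 81.

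**Assumptions.** The responder rate is not given, so 30%, 40% and 50% are used. Sensitivity and specificity are both set equal to the true BACC.

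**Dummy.** Sensitivity and specificity are 1 and 0 (or 0 and 1), so BACC = (1 + 0)/2 = 0.50.

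**Standard error.** SE = 0.5·√[s(1−s)/n₁ + t(1−t)/n₀], with s the sensitivity, t the specificity, n₁ responders and n₀ nonresponders. For n = 81 and 40% responders (32 and 49), at 0.67: 0.5·√[0.2211·(1/32 + 1/49)] = 0.0534. The 95% interval is 0.67 ± 1.96·0.0534 = 0.565 to 0.775. Over all six combinations of n and responder rate, the SE at 0.67 is 0.050–0.057. The widest interval is 0.558 to 0.782 and the narrowest 0.573 to 0.767.

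**Pass probabilities for one model.** These come from the exact product of two binomials, with the range over n = 81 and 90 and responder rates of 30–50%.

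| True BACC | Estimate above 0.50 | Estimate at least 0.67 |
|---|---|---|
| 0.50 | 46–50% | 0.2% or less |
| 0.55 | 80–82% | 1–2% |
| 0.60 | 95–97% | 8–12% |
| 0.62 | 98–99% | 15–19% |
| 0.65 | above 99% | 33–37% |
| 0.67 | above 99% | 48–51% |

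**If one pass among four counted.** This is a reading the text leaves open. The simulation used 10,000 runs of four equally good models, with between-model latent correlation from 0 to 0.9. At least one reaches 0.67 with probability 3–8% at true 0.55, 17–39% at 0.60, 30–59% at 0.62 and 55–85% at 0.65. At least one of four no-skill models exceeds 0.50 with probability 68–94%.

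**Using the lower 95% limit instead** (Wald limit as a stand-in for the bootstrap limit).
- Lower limit above 0.50: a no-skill model passes in about 2–3% of cases.
- Lower limit at or above 0.67: the observed BACC must be about 0.76–0.77. At 40% responders, one model passes in 1.4–1.7% of cases at true 0.65, 40–42% at 0.75 and 79–82% at 0.80. At true 0.70 it passes in 10–12% over the 30–50% range.

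**The case against.** A reader might infer that a pass by any one of four models settles the matter, that inadequate models will therefore often be called useful, and that beating the dummy is close to automatic. The documents do not support this. Model Interpretation judges each model, and the abstract and Objective of the Study speak of the models collectively. No sentence picks the best of four or makes one pass sufficient. Taken singly, a model at true BACC 0.60 reaches 0.67 in only 8–12% of cases and one at 0.55 in 1–2%. A no-skill model beats the dummy about half the time, which is far from automatic. These objections stand and limit the claim to what the table shows.

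That a model exactly at 0.67 fails about half the time is a property of any point-estimate cut-off and does not by itself show that the test set is too small.

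Uncertainty is not ignored altogether either: the planned bootstrap will yield an interval for each model. If the dummy were among the models compared, its interval would collapse to 0.50, and the non-overlap rule would then supply a proper test of the first aim. The article does not say so, and neither aim refers to an interval.

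Strengths and Limitations concedes the modest sample and the lack of external validation, and Comparison to Prior Work asks for validation and implementation trials. This lessens the consequence of a wrong label but does not change the rule that assigns it.

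Finally, Background presents 67% as a proposed benchmark. Whether it was meant for a point estimate or a lower limit cannot be seen from the article, so insisting on the lower limit would be a choice and not a correction.

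**Conclusion.** The concern holds in limited form. Each of four classifiers is judged on a point estimate with a standard error of about 0.05–0.06, so an observed 0.67 is compatible with true values from about 0.56 to 0.78. The dummy criterion discriminates poorly: one no-skill model meets it in 46–50% of cases. It also adds nothing for a model that meets the second criterion, since 0.67 already exceeds 0.50. The usefulness criterion is met by a single model in 8–12% of cases at true BACC 0.60 and 33–37% at 0.65. The risk is therefore material for models moderately or slightly below the benchmark and small for those near no skill. It would be larger if one pass in four counted, and the article should say whether it does.

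The figures rest on an assumed responder rate of 30–50%, sensitivity equal to specificity and 81–90 test patients. The four-model figures also assume equally good classifiers and a between-model correlation that the article does not give.

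**What to change.** 1. Before the test set is opened, name one primary classifier by its cross-validated BACC in the training set, and treat the other three as secondary. That cross-validation is already planned.
2. Claim superiority to the dummy only if the lower 95% bootstrap limit of the primary model's BACC exceeds 0.50.
3. Report the bootstrap interval beside the 0.67 benchmark for every model. When the point estimate reaches 0.67 but the lower limit does not, word the conclusion as 'benchmark reached, not established' in place of 'clinically useful'.

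The 5000 bootstrap samples already supply the limits, so no new computation is needed. The article states that the data had not been analysed for this study as of March 2025, so at that date the rule could still be set in advance.

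The cost is a less favourable claim. A lower limit of at least 0.67 should not become the sole pass/fail criterion: it would need an observed BACC of about 0.76–0.77, and a model truly at 0.70, above the benchmark, would pass only 10–12% of the time.
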